The limitations in both studies included problems of adherence to the interventions. Dropout rates were high, ranging from 14.8% [14] to 31.6% [13]; in the study by Arean et al. [13], 57.9% did not even download the assigned intervention app and the level of compliance with homework assignments was not reported. These issues are fundamental because individuals who leave the intervention show worse results and less satisfaction with the therapy, and when evaluating the efficacy of interventions, high dropout rates can lead to bias due to attrition, limiting the generalizability of the results [15]. In addition, homework completion is a significant predictor of therapy outcomes in various populations and interventions [16], including depression prevention interventions in the caregiver population [17]. This shows that when more homework is completed, the therapy results are better, leading to a greater reduction of depressive symptoms [17]. Complementing the interventions implemented through smartphones with a telephone conference call (TCC) to give feedback could help solve these problems. In behavioral skills training procedures, feedback is specifically defined as delivery of praise for correct performance of a target behavior and further instruction following incorrect performance [18].

The objectives of the present study are to (1) assess the efficacy of a cognitive behavioral intervention for indicated prevention of depression in informal caregivers, administered through a smartphone app (CBIA) with and without TCCs with respect to a care control group, (2) analyze the mediators of change in depressive symptoms, and (3) assess adherence and satisfaction with the interventions. As a central hypothesis, both interventions are expected to significantly reduce the incidence of depressive episodes and depressive symptoms compared to the control group at post-treatment and at 1-, 3-, 6-, and 12-month follow-up. Secondary hypotheses are (1) that the change in reinforcement and in negative automatic thoughts will mediate the effects of both interventions and (2) that the participants receiving CBIA + TCC will show greater adherence and satisfaction with the intervention than those who receive CBIA alone.

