## Methods

### Design

A randomized controlled clinical trial will be conducted to study the efficacy of a cognitive behavioral intervention for non-professional caregivers with elevated depressive symptoms administered through a smartphone app with and without TCCs. Specifically, eligible participants will be randomly assigned to one of three conditions, as follows: (1) CBIA; (2) CBIA + TCC; and (3) an attention control group (ACG).

The study phases are shown in Fig. 1. There will be six measurement points in the three groups (i.e., pre-treatment, post-treatment, and follow-up at 1, 3, 6, and 12 months). After the baseline assessment (pre-treatment), and once caregivers who meet the eligibility criteria are selected and interventions are administered, a post-treatment evaluation and four follow-ups will be performed (at 1, 3, 6, and 12 months). To minimize the loss of participants, we will follow the strategies recommended by Grady et al. [19], such as selecting participants who are likely to adhere to the intervention, obtaining various means to contact the participants (address, telephone, email), and making the intervention easy.

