To be included in the study, participants must meet the following inclusion criteria: (1) be a non-professional caregiver of a dependent family member whose dependency is officially recognized by the Regional Government of Galicia; (2) have a smartphone; (3) present a clinically significant symptomatology defined as a score equal to or greater than 16 in the Spanish version of the Center for Epidemiologic Studies Depression Scale (CES-D [20]); (4) not meet the diagnostic criteria for a major depressive episode according to the Diagnostic and Statistical Manual of Mental Disorders (DSM-5) [21]; (5) not have a history of major depression; (6) commit to participating in all evaluations; and (7) provide written informed consent. Participants who meet the following criteria will be excluded: (1) receiving psychological or psychopharmacological treatment in the last 2 months; (2) have other disorders that may act as confounding variables (e.g., symptoms due to substance use); (3) have severe psychological or medical disorders requiring immediate intervention (e.g., suicidal ideation) or that make the study impossible (e.g., significant cognitive impairment); (4) that the person in a situation of dependence has a severe or terminal prognosis within the next 14 months; or (5) that in the next 14 months they plan to move or to institutionalize the dependent they were caring for.

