### Statistical analyses

We will use the statistical package SPSS for Windows (version 21.0) for the analysis of the data. All analyses will be performed according to the intent-to-treat principle. If participants drop out from the study, the lost values ​​will be imputed using multiple imputation [33].

To analyze the incidence of depressive episodes in each of the measurement times (post-treatment, 1, 3, 6, and 12 months of follow-up), a global χ^2^ test will be performed to compare the three groups. If the differences are statistically significant (*p* < 0.05), pairwise comparisons will be performed using logistic regression. The relative risk and the required number of patients to be treated will be calculated following the formulas proposed by Guyatt et al. [34]. In addition, the time it will take participants to undergo a major depressive episode will be analyzed using a survival analysis. The analysis of the effect of the interventions on the outcome variable ‘depressive symptoms’ will be performed using two-way ANOVA with repeated measures. The analyses related to the effects of moderation or mediation will be carried out as per the recommendations of Baron and Kenny [35]. The model to evaluate moderation will include, as an independent variable, the type of treatment, the moderating potential, and the interaction between the two. An optimal combined moderator will also be sought according to Kraemer’s recommendations [36]. For the analysis of the mediation, we will perform adjustment of three regression equations to assess the effect (1) of the predictor variable (amount of treatment) on the dependent variable (change in depressive symptomatology after the intervention), (2) of the predictor variable in the mediator potential of the predictor variable (change in reinforcement and negative thoughts), and (3) of the mediator potential of the dependent variable, controlled by the predictor variable. Dropouts and adherence to interventions will be analyzed using a χ^2^ test to compare the percentage of dropouts and using an independent *t* test to compare the number of modules completed and the register of the intersessional tasks. Likewise, the level of satisfaction with the interventions will be assessed using the CSQ-8 through a frequency analysis and descriptive statistics, and both active conditions will be compared at post-treatment using an independent *t* test.

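### The three mediation regressions are written in change scores with no pre-treatment score as covariate, so correlated baselines can give a spurious mediator coefficient; adding the baselines is nearly free

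*Protocol article*

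**What the plan says.** The Statistical analyses section of the protocol article announces that "we will perform adjustment of three regression equations to assess the effect", and then names the terms:

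- Equation 1: the effect "of the predictor variable (amount of treatment) on the dependent variable", where the dependent variable is "change in depressive symptomatology after the intervention".
- Equation 2: the effect of the same predictor on the candidate mediators, given as "change in reinforcement and negative thoughts".
- Equation 3: the effect "of the mediator potential of the dependent variable, controlled by the predictor variable".

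No pre-treatment score is listed in any equation. The baselines will exist: the Design section says "There will be six measurement points in the three groups (i.e., pre-treatment, post-treatment, and follow-up at 1, 3, 6, and 12 months", and CES-D, EROS and ATQ are all listed outcomes.

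The equations serve objective 2 and the secondary hypothesis "that the change in reinforcement and in negative automatic thoughts will mediate the effects of both interventions". Entry itself depends on the CES-D, since caregivers must "present a clinically significant symptomatology defined as a score equal to or greater than 16 in the Spanish version of the Center for Epidemiologic Studies".

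**The concern.** A change score is negatively correlated with its own starting value whenever the pre-post correlation is below 1. Caregivers with many negative thoughts at baseline are likely to have a high CES-D at baseline too. Both scores then tend to fall back together, whether or not one drives the other. Regressing change on change, controlling only for the predictor, attributes part of that shared fall to the mediator. The cause is a baseline variable that the trial measures and could condition on.

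With the expected signs (ATQ positively and EROS negatively related to CES-D), the spurious coefficient points the way secondary hypothesis 1 predicts. At stake is a claim about how the intervention works. A smaller matter is that equations 1 and 2 estimate treatment effects less precisely from change scores than from the same model with the baseline as covariate.

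**Working it through.** **The plan's own figure.** The only planned size is for the primary outcome: 49/0.85 = 57.6, rounded up to 58 per group, and 3 × 58 = 174. It reproduces. Nothing is stated for mediation, so what follows shows how the equations behave.

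**Inputs.** From the article: the form of the equations; 58 per group (two arms, N = 116); 49 per group after attrition; CES-D ≥ 16; 39% to 44% of caregivers with elevated symptoms. Assumed: pre-post correlation ρ of 0.3 to 0.7; baseline mediator/CES-D correlation r of 0.4 to 0.6 before selection; treatment effects of 0.5 SD on mediator and outcome; no true mediator-outcome effect. The two randomised arms stand in for amount of treatment.

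**Step 1: bias without selection.** With unit variances, M1 = ρM0 + treatment + e1 and Y1 = ρY0 + treatment + e2, where e1 and e2 are independent. Given treatment:

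- Cov(ΔM, ΔY) = (1−ρ)²r
- Var(ΔM) = (1−ρ)² + (1−ρ²) = 2(1−ρ)
- spurious coefficient = r(1−ρ)/2

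At ρ = r = 0.5 this is 0.125. It is zero when r = 0.

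**Step 2: effect of the entry cut-off.** A cut-off at +0.2 SD leaves 42% above it, matching 39% to 44%. The mean of the selected group is λ = 0.391/0.421 = 0.929 SD above the population mean. The remaining baseline CES-D variance is v = 1 − 0.929 × (0.929 − 0.2) = 0.322. If selection acts on a separate screening score correlated 0.7 with baseline, v = 1 − 0.49 × (1 − 0.322) = 0.668. The covariance becomes (1−ρ)²rv, and Var(ΔM) becomes (1−ρ)²[1 − r²(1−v)] + (1−ρ²).

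At ρ = r = 0.5:

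- no selection: 0.125/1.000 = 0.125
- separate screening score: 0.0835/0.979 = 0.085
- cut-off on the baseline itself: 0.0403/0.958 = 0.042

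The cut-off shrinks the bias. The correlation of CES-D change with its own baseline likewise weakens, from −0.50 to −0.31 at ρ = 0.5.

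**Step 3: error rates.** Simulation at N = 116, two-sided 5%, over the assumed ranges:

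| Where selection acts | Equation 3 significant | All three steps significant |
|---|---|---|
| On the baseline CES-D itself | about 6-13% | about 4-6% |
| On a separate screening score (0.7) | about 9-36% | about 7-16% |
| Baselines added | about 5% | about 2-5% |

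The formulas agree. With k = (1−ρ)²rv / √(Var ΔM · Var ΔY), Var(ΔY) = (1−ρ)²v + (1−ρ²) and noncentrality k√113/√(1−k²), the extreme settings are:

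- Baseline cut, ρ = 0.7, r = 0.4: k = 0.021, noncentrality 0.22, rejection 6%.
- Baseline cut, ρ = 0.3, r = 0.6: k = 0.081, noncentrality 0.86, rejection 14%.
- Separate screening, ρ = 0.7, r = 0.4: k = 0.041, noncentrality 0.44, rejection 7%.
- Separate screening, ρ = 0.3, r = 0.6: k = 0.152, noncentrality 1.64, rejection 37%.

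The small gaps from the table are within what simulation error and the normal approximation allow.

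**Step 4: precision of equations 1 and 2.** The variance factor is 2(1−ρ) for change and 1−ρ² with baseline adjustment. With 49 per arm, 0.5 SD, randomised arms and no truncation, at ρ = 0.5:

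- change: 0.5/√1.00 × √(49/2) = 2.475; 2.475 − 1.96 = 0.515; power 70%
- adjusted: 0.5/√0.75 × √(49/2) = 2.858; 2.858 − 1.96 = 0.898; power 82%

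At ρ = 0.6 the figures are 79% and 87%. In simulations of all three arms with the baseline cut-off applied, the loss at ρ = 0.4 was about 3-5 points on the outcome path and 7-13 on the mediator path. At ρ = 0.8 it was close to zero.

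**The case against.** **The text is condensed and does not exclude baselines.** It says change, without calling it raw or residualised. A reader might infer that the plan rules out baseline covariates; it does not say so, and a fuller plan could list them. What remains is that the article writes out all three equations with predictor, dependent variable, mediators and control, so the comment concerns a stated model. Ordinary change is the natural reading.

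**The entry criterion.** A reader might infer that selecting on CES-D ≥ 16 makes the problem worse through regression to the mean. It does not. The average fall goes into the intercept, and the narrower baseline range reduces the bias (step 2). Simulations without the cut-off give 19-36% at ρ = 0.5 and 31-64% at ρ = 0.3; these leave out the trial's own entry rule and should not be quoted as its error rate.

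**Which score is truncated is open.** The section on participants and recruitment describes a screening call that evaluates depressive symptoms, followed by a full evaluation in the app, and the Outcomes section has self-administered scales completed there. That suggests a separate screening score, hence the upper range, but the article does not settle it.

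**Equation 3 alone does not establish mediation.** Under the Baron and Kenny steps a treatment effect on the mediator is also needed; without one, false mediation occurred in 0.3% of simulated trials. This objection stands, and the joint rates are the ones to weigh.

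**Change score against covariance adjustment is a matter of efficiency.** Under randomisation the treatment comparison is unbiased either way. That stands for randomised arms. The stated predictor is amount of treatment, which is not clearly the arm, so baseline balance across its levels cannot be assumed.

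**Conclusion.** The point holds as a free or cheap improvement to a secondary analysis. As written, and read as ordinary change scores, equation 3 can yield a spurious mediator coefficient. Under the stated assumptions its false-positive rate is about 6-13% if the entry CES-D is the baseline and about 9-36% if a separate screening score is used. The rate for all three steps together is about 4-6% or 7-16%, against 2-5% with baselines, so the excess is slight in the first case and material only in the second. The gain in power for equations 1 and 2 is real at moderate pre-post correlation, shrinks under truncation and nearly vanishes at 0.8.

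Every rate depends on correlations the article does not give, and on two randomised arms standing in for amount of treatment. A reader might extend the point to the efficacy results; the documents do not support that. Depression incidence and the repeated-measures analysis of CES-D do not use these equations. Only objective 2 and secondary hypothesis 1 are affected.

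**What to change.** In the Statistical analyses section, state that each of the three mediation regressions includes the pre-treatment score of its dependent variable, and that equation 3 includes both the pre-treatment CES-D and the pre-treatment score of the mediator under test (EROS or ATQ). Modelling the later score with the same baselines as covariates is equivalent. If the full plan already does this, saying so in the section settles the point.

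The cost is one sentence and one or two degrees of freedom per model, with no new data or participants. The mediator coefficient will probably be smaller. Measurement error in the baseline scales can leave some residual confounding, so the adjustment reduces the problem without guaranteeing its removal.

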### Monitoring

A Data Monitoring Committee (DMC) will be established to monitor and guarantee the correct execution of the study, which will be independent of the organizers of the study and can order an independent audition once a year. The steering committee, led by the principal investigator, will follow the principles of good clinical practice, including quality control of the clinical protocol, data management, and team meeting organization. A confidential annual report on the development of the trial will be sent to the DMC.

A pilot study will be conducted to assess the feasibility of the study. Any significant protocol modification that may affect the performance of the study, the potential benefit to or safety of the patient, including significant changes in study design, population, sample size, or study procedures, will require a formal amendment to the protocol, which will have to be approved by the Bioethics Committee prior to its implementation.

In addition, an independent statistician will conduct a preliminary analysis after the pilot study and when 50% of patients have been randomized and have completed follow-up. The statistician will inform the independent DMC, who will have access to all data and will discuss the results of the analysis with the steering committee at a joint meeting. The steering committee will then decide on the continuation of the trial and report to the Bioethics Committee. Any solicited or spontaneous reported adverse event through the study will be notified to the steering committee, who will take the necessary actions.

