### Sample size

Based on a previous study of indicated prevention of depression in caregivers [9], which involved the same program that will be evaluated in the present study (albeit in person), we estimate that a sample size of 49 participants per group (98 in total) would be sufficient to detect an 18.6% difference in the incidence rates of major depression episodes between the experimental group and the control, assuming a two-tailed test α of 0.05 and a power (1 – β) of 0.80. However, considering an attrition rate of approximately 15% based on studies that have evaluated the use of interventions for the treatment of depression applied through an app [14], we estimate that the number of participants per group should be 58, resulting in a final sample size of 174.

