### Trial status

Recruitment start: September 28, 2018.

Study completion: December 29, 2019.

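### Interim results are to be discussed with the investigator-led steering committee, which then decides on continuation, with no stated rule protecting the 0.05 and, on the stated dates, too late to change much

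*Protocol article*

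**What the plan says.** The Monitoring section of the protocol article sets up an independent DMC and plans two looks: "an independent statistician will conduct a preliminary analysis after the pilot study and when 50% of patients have been randomized and have completed follow-up". Both are reported to the DMC, "who will have access to all data and will discuss the results of the analysis with the steering committee at a joint meeting". The decision is then placed outside the DMC: "The steering committee will then decide on the continuation of the trial and report to the Bioethics Committee". The same section describes that committee: "The steering committee, led by the principal investigator, will follow the principles of good clinical practice". Of the pilot it says only: "A pilot study will be conducted to assess the feasibility of the study".

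The section names no purpose for the looks (efficacy, futility or safety) and no stopping criterion. The Sample size section works with the full error rate, "assuming a two-tailed test α of 0.05 and a power (1 – β) of 0.80". The Statistical analyses section applies the same level to the global test of the three groups at each time point: "If the differences are statistically significant (*p* < 0.05), pairwise comparisons will be performed using logistic regression".

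Trial status gives 28 September 2018 as the start of recruitment and then "Study completion: December 29, 2019". The intervention takes about 5 weeks and the last assessment is at 12 months.

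**The concern.** An independent DMC exists so that the people running a trial do not learn comparative results while data are still coming in. Here the DMC passes the results on to the committee led by the principal investigator, and that committee makes the decision. Those who oversee the remaining 12-month assessments, retention and the final analysis would know how the comparison is going.

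Two further matters hang on the same paragraph. First, a decision to continue or stop follows from the interim results, while the sample size and the final test both use the whole 0.05. If stopping for benefit were possible, the overall error would exceed 0.05 unless a boundary applied. Second, a 50% look that waits for completed follow-up may come so late that the decision has little left to act on.

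**Working it through.** **1. The plan's own sample size.** Allowing for 15% attrition, 49 / (1 − 0.15) = 57.6, rounded up to 58, and 58 × 3 = 174. Both figures reproduce. The 49 cannot be checked outright because only the difference of 18.6 points is given, not the two rates. With a fixed-sample two-proportion formula (pooled variance, two-sided 0.05, power 0.80, no continuity correction) and assumed rates, n per group is:
- 0% vs 18.6%: 38
- 3.0% vs 21.6%: 48
- 4.0% vs 22.6%: 52
- 10% vs 28.6%: 70

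So about 3% vs 22% gives 49 at the full 0.05 with no allowance for interim looks, and the article mentions none.

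**2. Who sees what, and who decides.** The statistician and the DMC are independent. The next two sentences of the section take the results to a joint meeting and give the continuation decision to the steering committee. Nothing there limits the discussion to safety, to pooled data or to a bare recommendation. A charter that kept results from the steering committee would contradict this text, so the text itself has to change.

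**3. Type I error if a look could stop for efficacy at 0.05.** For one comparison with interim information fraction t, the error is P(|Z₁| > 1.96 or |Z₂| > 1.96), where the correlation of Z₁ and Z₂ is √t. Simulation with 4 million draws gives:
- t = 0.50 (12-month completers only), correlation 0.707: 0.083
- t = 0.87 (assumed): 0.067
- t = 0.90 (assumed): 0.065
- t = 0.95 (assumed): 0.061

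The last three cover a look that uses all data then available. Two-look boundaries at t = 0.50 that hold the error at about 0.05 are:
- O'Brien-Fleming type: p < 0.0052, then p < 0.048
- Pocock type: p < 0.0294 at both looks
- Haybittle-Peto: p < 0.001, then 0.05 (overall 0.0503)

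Looks confined to safety or futility do not raise the error.

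**4. Calendar.** From 28 September 2018 to 29 December 2019 is 457 days. Even accrual is assumed, and completed follow-up is read as the 12-month visit.

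| | Follow-up counted from end of treatment | Follow-up counted from randomization |
|---|---|---|
| Enrolment window | 457 − 35 − 365 = 57 days | 457 − 365 = 92 days |
| Randomizations per week | 174 / (57/7) = 21.4 | 174 / (92/7) = 13.2 |
| Last randomization | 24 Nov 2018 | 29 Dec 2018 |
| Last treatment ends | 29 Dec 2018 | 2 Feb 2019 |
| Half have completed 12 months | 30 Nov 2019 | 13 Nov 2019 |
| Days left to stated completion | 28.5 | 46 |

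On either count, everyone has been randomized and treated more than nine months before the 50% look. Before attrition, 174 / 2 = 87 participants would still have a 12-month assessment to come.

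**The case against.** The strongest reply is that the article never says a look may stop the trial for benefit. It speaks of a preliminary analysis and of continuation. Boundaries are commonly left to the full protocol, the SAP or a DMC charter, none of which is shown. This stands. A reader might infer that error control is lost, but the documents do not support that: the 8.3% needs an efficacy stop at p<0.05 on 12-month completers alone. Nor do they support counting the pilot look as a further test at 0.05. The pilot is tied to feasibility, and the article does not say that it compares arms or that its participants count among the 174.

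A second reply is that knowledge in the steering committee need not reach the outcome. The Outcomes section has the diagnostic interview done by assessors blind to the objectives, the interventions and the allocation, and the CES-D is completed by participants in the app. This limits the route to bias, so a reader should not infer that the remaining interviews would be biased. It does not restore confidentiality, because those leading the trial would still hold interim results. The article also does not state in what form the committee sees them. Access to all data describes the DMC, so disclosure by arm is the natural reading but not an explicit one.

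Third, the timing argument rests on a completion date that itself looks hard to meet, and the article does not define completion. With longer enrolment the look could come while participants are still being recruited or treated. That is correct, but then the stated date is wrong and the disclosure matters more. One of the two must be corrected.

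**Conclusion.** The governance point holds on the text alone: interim results go to the investigator-led committee, which takes the decision, while outcome assessments are pending. It needs no assumption about unseen documents.

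The error-control point holds only conditionally. No rule stated in the article protects the full two-sided 0.05. If the 50% look could stop the trial for efficacy at p<0.05, the error for one comparison would be about 8.3%, or about 6–7% on an assumed 87–95% of the information.

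The timing point holds given the stated dates, even accrual and the 12-month visit as the end of follow-up: 57 or 92 days for enrolment, and a 50% look in mid to late November 2019 that can change little.

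Taken together this is a moderate matter that should be corrected. Blinded interviewers and the silence on efficacy stopping keep it from being a fatal flaw.

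**What to change.** Amend the Monitoring section as follows.
- Interim results by arm are seen only by the independent statistician and the DMC, in closed session.
- The DMC gives the steering committee only a recommendation (continue, modify or stop), accompanied by pooled data.
- The looks are limited to safety, data quality and retention.
- If stopping for efficacy is intended, the protocol says so and states a boundary. Haybittle-Peto at p<0.001 leaves the final test at about 0.05.

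Reconcile the timing of the 50% look and the completion date in Trial status with 5 weeks of intervention and 12 months of follow-up, and say what study completion means.

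The cost is wording in the protocol and the DMC charter, with no added participants. The steering committee gives up seeing interim results by arm.
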